In a novel study by Cormie et al. [10], which evaluated the effect of low- and heavy-load resistance exercise among a sample with BCRL, lymphedema status and lymphedema symptoms remained stable immediately after exercise, and 24- and 72-hours after exercise, irrespective of load. While these findings provide important information for women with BCRL, the purpose of this study is to determine acute changes in extracellular fluid, arm volume and associated lymphedema symptoms after a session of low- and heavy-load resistance exercise in women at risk for BCRL. It is hypothesized that no interlimb differences in extracellular fluid, arm volume or lymphedema-associated symptom severity will be observed over time or between resistance exercise loads.

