### Sample size and analytical plan

The sample size calculation is based on changes in L-Dex scores between baseline and 72 h post-resistance exercise sessions. From results of Cormie et al. [10] we hypothesize the standard deviation in the distribution to be 1.9 units. No published normative change scores exist for the at-risk population, as well as no evidence regarding a threshold for a clinically significant acute change. For patients with BCRL a change score of 2L-Dex units is considered clinically relevant based on clinical experience. We believe that an L-Dex of 2 units is too conservative in the at-risk population, and have therefore set a threshold at 3L-Dex units. Thus, if there is no difference between groups, then 18 patients are required to be 90 % sure that the limits of a two-sided 90 % confidence interval will exclude a difference in means of more than 3.0. To allow for possible drop-outs we plan to include 20 patients.

Data will be analyzed using the Statistical Package for Social Sciences (SPSS) software (version 19) for Windows (IBM SPSS, Chicago, IL). Analysis will include standard descriptive statistics and both intention to treat and per-protocol analysis will be performed. Using a generalized estimating equations framework for continuous outcomes to determine time (baseline, pre-, post, 24- and 72 h) and intervention (low-/ heavy-load) effects, the interaction between time and intervention will be considered [23]. Two-tailed *p* < 0.05 will be taken as evidence of statistical significance.

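### The trial is hypothesised and sized for equivalence within 3.0 L-Dex units, but the analysis paragraph states only a two-tailed p < 0.05 difference test

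*Protocol article*

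**What the plan says.** The Background section of the protocol article states the hypothesis as one of no effect: "hypothesized that no interlimb differences in extracellular fluid, arm volume or lymphedema-associated symptom severity will be observed over time or between resistance exercise loads".

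Under Sample size and analytical plan, the first paragraph turns this into an equivalence target for the change in L-Dex from baseline to 72 hours. The authors "have therefore set a threshold at 3L-Dex units". For variability, "we hypothesize the standard deviation in the distribution to be 1.9 units", taken from a study of women who already had lymphedema. The stated target, for 18 patients and a true difference of zero, is being "90 % sure that the limits of a two-sided 90 % confidence interval will exclude a difference in means of more than 3.0". Twenty are to be enrolled to cover drop-out.

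The second paragraph under the same heading gives the analysis. Both intention-to-treat and per-protocol analyses are planned, with a generalized estimating equations model for time, load and their interaction. The only criterion given is "Two-tailed *p* < 0.05 will be taken as evidence of statistical significance". The 3.0-unit margin and the 90% interval do not appear in that paragraph.

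**The concern.** The two paragraphs answer different questions. The sizing paragraph asks whether the data rule out a difference larger than 3.0 units. The analysis paragraph asks whether the data rule out a difference of exactly zero. Rejecting zero can count against the Background hypothesis, but failing to reject zero cannot support it, because a non-significant result is also what imprecise data produce.

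Table 1 of the article lists the study type as safety, and the Discussion hopes to inform exercise prescription and risk-reduction advice. As written, the same data could meet the criterion the trial was sized on and also be reported as a significant difference between loads. The text does not say which finding governs the conclusion.

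**Working it through.** **Inputs from the protocol article:** margin 3.0 L-Dex; SD 1.9; assumed true difference 0; two-sided 90% interval; 90% power; 18 patients.

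**Assumptions added here:** 18 women analysed as a two-period cross-over with 16 degrees of freedom; 1.9 read as the SD of one session's change; correlation ρ between a woman's two changes of 0 or 0.5. The article gives no correlation. The calculations use the t distribution as an approximation to the planned model.

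**1. Reproducing the stated sample size.** The equivalence formula for two groups gives

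n per group = 2 × [1.9 × (1.645 + 1.645) / 3.0]² = 8.68, rounded up to 9, so 18 in total.

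This matches. A two-sided 5% superiority test to detect 3.0 units with 90% power also gives 9 per group, so the number alone does not identify the rule. The wording does: the aim is that the "confidence interval will exclude a difference in means of more than 3.0", under a true difference of zero.

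**2. Smallest significant difference at the planned SD.** SD of the within-woman difference = 1.9 × √(2(1 − ρ)); SE = that SD / √18; smallest significant difference = 2.120 × SE.

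- ρ = 0: SD 2.69, SE 0.633, smallest significant difference 1.34
- ρ = 0.5: SD 1.90, SE 0.448, smallest significant difference 0.95

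Both are less than half the margin.

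**3. How the rules can disagree.** Take an observed difference of 1.5 with SE 0.448. Then t = 1.5 / 0.448 = 3.35, above 2.120, so the result is significant. The 90% interval is 1.5 ± 1.746 × 0.448, or 0.72 to 2.28, wholly inside ±3. By simulation, with a true difference of 1.5, about 82% of trials (ρ = 0.5) or 35% (ρ = 0) are both significant and within the margin.

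**4. The opposite error.** Probability of p ≥ 0.05 when the true difference is 3.0 (non-central t). SDs other than 1.9 are assumptions.

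| SD of change | ρ = 0.5 | ρ = 0 |
|---|---|---|
| 1.9 (planned) | about 0% | 0.7% |
| 2.5 | 0.3% | 8% |
| 3 | 2% | 20% |
| 4 | 15% | 44% |

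The 90% interval rule declares equivalence in at most about 5% of trials at a true difference of 3.0, whatever the SD. At the planned SD the p-value is therefore not the more lenient of the two. The difference is that its error rate depends on the SD, while the interval rule's is bounded.

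**5. Power of the interval rule at n = 18, true difference 0.** At SD 1.9 it is above 99% for either correlation. At SD 4 it falls to about 84% (ρ = 0.5) or 40% (ρ = 0).

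**The case against.** The strongest reply is that the article never says a non-significant result will be taken as proof of no difference. A reader might infer that, given the hypothesis and the lack of another criterion, but the sentence on p < 0.05 reads as a general convention for all outcomes and model terms. The 90% interval stands under the same heading, and planning both intention-to-treat and per-protocol analyses is compatible with an equivalence reading. This stands as to intent. It does not remove the mismatch: the article states a criterion for its analysis, and it is not the one the trial was sized on. That differs from detail left to an unseen analysis plan.

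Two further stronger readings should be set aside. A reader might infer that a rise common to both loads would go undetected. It would not, because the planned model includes a time effect as well as the load contrast. A reader might also infer a large uncontrolled risk of false reassurance. Under the article's own SD that risk is below 1%; the 15% to 44% figures need an SD of 4, which the article does not give. A larger SD is worth examining, since 1.9 comes from a different population, the article says no normative change scores exist for women at risk, and its follow-up section notes highly variable responses. It remains an assumption.

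It is also fair that, at the planned SD, the error runs in the cautious direction, and that the Discussion calls the study exploratory and its evidence initial. This limits the harm. It does not make a difference test suitable for a no-difference hypothesis.

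**Conclusion.** The concern holds as a mismatch between the sizing criterion and the stated analysis criterion. At the planned SD its main effect is that differences of about 0.95 to 1.34 units, well inside the 3.0-unit margin, would be reported as significant. With a true difference of 1.5, 35% to 82% of trials would satisfy both rules at once and send opposite messages. False reassurance from a non-significant result is negligible at SD 1.9 and becomes material only with a clearly larger SD. These sizes rest on 18 women analysed, the assumed correlations of 0 to 0.5, and 1.9 being the SD of one session's change. The mismatch itself rests on none of them, and it bears on the primary conclusion.

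**What to change.** In the analysis paragraph, or the analysis plan before data are analysed, state the following:

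- The primary conclusion rests on whether the two-sided 90% confidence interval for heavy minus low in baseline-to-72-hour L-Dex change, from the planned model, lies wholly within ±3.0. This is required in both the intention-to-treat and per-protocol sets.
- The within-session change over time, already in the model as the time effect, is reported as an estimate with its interval. A formal equivalence test on the heavy-load session alone would be an addition, because the trial was not sized for it.
- Arm volume and symptom scores are reported as estimates with intervals. The p < 0.05 criterion is kept for secondary contrasts, and no conclusion of no difference is drawn from p ≥ 0.05.

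The cost is wording. The sample size of 18 stands, because it was derived for this rule. The one downside is that, if the SD proves larger than planned, the interval rule may be inconclusive at 18 women (power about 40% to 84% at an assumed SD of 4). That would reflect what such data can show.

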### Safety and ethical considerations

The treating oncologist will have the overall responsibility for the participants. All personal data will be treated in accordance with existing rules and regulations.

A full body DXA scan utilizes weak x-rays and is not considered dangerous [24]. In this study, since only arms will be scanned the radiation dose is estimated to be 0.0001 mSv for both arms. Eight scans result in a total dose of 0.0008 mSv, which is less than the background radiation an average person is exposed to in one day in Denmark.

As about 20 % of women treated for breast cancer develop BCRL [1], it is expected that some of the participants in this study will develop BCRL. Participation in this study involves regular assessment of the at-risk arm during the study period, using some of the best technology to date. This allows for early detection of BCRL, which in turn would render a better prognosis, as early detection is associated with a better outcome [4]. If participants develop signs of swelling or an L-Dex score persisting over one week during the familiarization or experimental study period, they will be referred to the treating oncologist for lymphedema treatment and will be withdrawn from the study.

A completed SPIRIT checklist is included as Additional file 1.

## Discussion

Participating in resistance exercise during adjuvant chemotherapy for breast cancer has been associated with increases in muscle strength [25–29], lean body mass [25, 28], and self-esteem [25], and has been found to mitigate fatigue and to maintain quality of life [29]. Furthermore, there is evidence to suggest that resistance exercise might be associated with a higher completion rate of planned chemotherapy [25]. Moreover, generalized edema characterized by an increase in the size of the interstitial compartment of extracellular fluid is a potential side effect to taxane-based chemotherapy [30, 31]. Thus, swelling as a consequence of increased fluid in addition to an impairment of lymph fluid transport, could potentially contribute to swelling of the at-risk arm. Hypothetically, this could be thwarted by resistance exercise due to increased lymph clearance likely through the effects of the muscle pump [32, 33], lending additional rationale for instigating resistance exercise during adjuvant chemotherapy.

To our knowledge, studies investigating the safety and efficacy of resistance exercise in patients at risk for BCRL have utilized low- to moderate-resistance exercise intensities [6, 7], with only one cross-sectional study [11] investigating heavy-load resistance exercise. Indeed, in a paper identifying the top 10 research questions related to physical activity and cancer survivorship, Courneya et al. [34] highlighted the need for studies investigating safety and optimal exercise prescription, and specifically the role of vigorous-intensity activity, as important research areas [34].

The rational for utilizing heavy-load resistance exercise is supported by exercise science literature that indicates that this higher training intensity can lead to additional benefits as a dose–response relationship exists between the load of resistance exercise and gains in muscular structure and function [35, 36]. Furthermore, breast cancer survivors may suffer from losses of bone mass (particularly those on aromatase inhibitors), at least in part as a result of the catabolic effects of treatment. Resistance exercise interventions with lower loads have not yielded significant training effects on bone mineral density [27, 37]. It has been postulated that the absence of a measurable effect on bone mass density is related to the adaptive nature of bone that requires heavier loads [37], as heavy-load resistance exercise has been identified as an osteogenic exercise modality in women without cancer [38]. Thus, establishing the safety of heavy-load resistance exercise is prudent and of significance for the breast cancer population.

No standardized measurement method exists to diagnose or monitor BCRL [1, 20, 21], with a variety of techniques and definitions used. Early BCRL is characterized by an increase in extracellular fluid. Indirect measurement methods such as circumference, water displacement, and perometry measure volume of the entire limb to detect small changes in extracellular fluid which accounts for approximately 25 % of the total limb, and do not differentiate between tissue types [5, 18]. In contrast, BIS directly measures lymph fluid change by measuring the impedance to a low level electrical current allowing for a sensitive [21, 39] and reliable measurement method to detect extracellular fluid changes among at-risk breast cancer survivors [39]. Furthermore, BIS is fast and easy to administer, and as impedance measures are reported as an L-Dex value, inherent volume differences associated with hand dominance are taken into account [5, 39]. However, BIS loses its sensitivity to monitor BCRL over time as lymphedema progresses into later stages, whereby the excess extracellular fluid initially characterizing BCRL is replaced with adipose tissue [5, 21].

DXA is another measurement method that can differentiate between tissue types giving an estimate of BMC, fat mass and lean mass where the lean mass component includes extracellular fluid [20, 21, 40]. DXA has been found to be sensitive to changes in tissue composition, making it an ideal measurement method to monitor BCRL over time as fluid components are replaced with adipose tissue. Furthermore, DXA allows for analysis of separate regions of the arm, of potential clinical importance for patients where swelling is confined to a specific region of the arm or hand [20, 21, 40, 41]. In this study we scan the arms separately and use software with a high resolution allowing for more precise definition of ROIs and the possibility to define bone and soft tissue manually as described by Gjorup et al., with a low inter-rater variation (ICC ≥,9990) [20]. To the authors’ knowledge, this is the first time that DXA, with this software, will be used to detect volume changes in the BCRL at-risk population adding new insights into the application of this measurement method.

This exploratory study utilizes a cross-over design to determine acute changes in extracellular fluid and arm volume. This design lends more statistical power, with the practical advantage of a smaller sample size, as between-patient variation is inherently eliminated [42], providing a framework for an efficient comparison between the two resistance exercise loads. However, this study can only provide us with information regarding extracellular fluid and arm volume changes after one resistance exercise session, limiting the generalizability to repeated resistance exercise training and long-term effects on arm volume. Nonetheless, this study can lend initial evidence regarding the safety of heavy-load lifting and can help guide future studies and optimal exercise prescription.

Finally, women at risk for BCRL still receive risk reduction advice including avoiding heavy lifting [43, 44]. This advice can lead to women being apprehensive about lifting heavy loads with consequences for daily living (e.g., not lifting children, groceries, etc.). However, this advice is not based on research and knowledge gained from this study can provide a preliminary evidence base for guiding risk reduction practices involving intermittent heavy-load activity necessary for daily living.

## Abbreviations

AND, axillary lymph node dissection; BCRL, breast cancer-related arm lymphedema; BIS, bioimpedance spectroscopy; CTC, common toxicity criteria; DXA, dual-energy x-ray absorptiometry; ICC, intraclass correlation coefficient; L-Dex, lymphedema index; ROI, region of interest
